### Intervention

Clinical assessments will be performed at baseline (T0) and at the end of 4 weeks (T1), consisting of a symptom-limited cardiopulmonary test, 6MWT, quality of life assessment, and laboratory tests (Table 1).

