### Sample size

For the sample size estimation, the following main outcome was *the* distance covered in the 6MWT. As there are no studies that have previously evaluated these outcomes, we used Du et al. [7] as the parameter of the minimal clinically important difference (MCID) value of 6 WMT in HF patients. The increase of 30 m was described as the mean value among studies. To calculate the effect size in the present study, we accepted 30 m of physical capacity improvement as the MCID to the control group (sham-tDCS during aerobic exercise) and, empirically, we chose 45 m of physical capacity improvement as the MCID to the experimental group (anodal tDCS during aerobic exercise). The effect size calculation was 0.41 Cohen’s *F* value. Therefore, we used the following parameters as sample size calculations for the ANOVA two-way test between factors: effect size of 0.41 by Cohen’s *F*, *α* = 5%, *β* = 80%, 2 groups and 2 measurements, and correction between measurements of 0.5. A total of 38 volunteers were reached,however, with the possibility of sample loss of 20%, a sample of 44 participants was estimated, 22 for the experimental group and 22 for the control group. For the calculation, the statistical program G*Power 3.1 (University of Dusseldorf, Dusseldorf, Germany) was used.

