### Statistical analysis

Exploratory analyses will be carried out allowing a survey of the frequency distribution and calculation of means and standard deviations. The 95% confidence intervals will be considered, and effect sizes will be calculated for primary and secondary outcomes. Statistical significance will be stipulated with *p*<0.05. The Shapiro-Wilk test will be applied to analyze the normality of the sample distribution; unpaired *t*-test will be used for numeric variables, comparing means between two groups; and Fisher’s exact test will be used for categorical variables. Two-way ANOVA for between factors accompanied by post hoc Bonferroni analysis will be used to measure and predict the degree of relationship between inter- and intragroup variables. Pearson correlation will be performed to test the association between two continuous variables, and multiple linear regression will be used to quantify the relationship between predictor variables and the outcome variable. For data analysis, the statistical programs Jamovi (Jamovi Project, Sydney, Australia) and GraphPad Prism 7.0 (GraphPad, CA, USA) will be used. We will not perform sub-analysis, mainly because the primary stage is well defined in relation to the central question. Furthermore, it may be necessary to perform adjusted calculations for some variables, such as age, weight, BMI, EF%, and β-blocker drug dose. For this purpose, the utilization of these variables as covariates will be used in the ANOVA two-way analysis described above.

Participants who discontinue or deviate from intervention protocols will have their data on 6MWT and inflammatory cytokines collected.

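### The 80% power behind 38 completers belongs to a test that averages over baseline; on the plan's own effect size and correlation, group-by-time has about 69% and the averaged group effect about 30%

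*Protocol article*

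**What the plan says.** The primary outcome is 6-minute walk distance, measured at baseline and after 4 weeks. For its effect size, the Sample size section says "we accepted 30 m of physical capacity improvement as the MCID to the control group" and, for the other arm, "we chose 45 m of physical capacity improvement as the MCID to the experimental group". From these it reports Cohen's f = 0.41 without giving a standard deviation.

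The calculation is described as "parameters as sample size calculations for the ANOVA two-way test between factors: effect size of 0.41", at a 5% significance level and 80% power (printed as beta), with "2 groups and 2 measurements, and correction between measurements of 0.5". I read the word correction there as correlation. The result is "A total of 38 volunteers were reached", raised to 44 for a possible 20% loss.

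The Statistical analysis section uses the same label: "Two-way ANOVA for between factors accompanied by post hoc Bonferroni analysis will be used". It does not say which term of that ANOVA answers the primary question. The optional covariates it lists are age, weight, BMI, ejection fraction and beta-blocker dose. Baseline 6MWT is not among them.

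**The concern.** A repeated-measures ANOVA with two arms and two time points yields a group effect, a time effect and a group-by-time effect. The between-factors routine powers the first, which compares the arms on the mean of each patient's two measurements. It assumes that the full effect is present in both.

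Here one of the two measurements is taken before treatment, when randomised arms have no expected difference. The effect size describes a difference in improvement, so it appears only at week 4. An effect defined on change has been entered in a routine that dilutes it with baseline, while the routine's variance formula still credits the baseline measurement as extra information on the treatment effect.

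This is the only power justification for the primary outcome. A null result would be read against a claimed 80% that the named analysis does not have on the plan's own figures.

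**Working it through.** **Inputs (Sample size section).** Improvements 30 m and 45 m; f = 0.41; alpha 5%; power 80%; 2 groups; m = 2 measurements; r = 0.5; N = 38 completers, 44 enrolled, 20% loss. The 1:1 allocation is in the Study design section.

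**Derived, not stated.** With two equal groups d = 2f = 0.82, so the implied SD is 15 / 0.82 = 18.3 m.

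**1. Reproduce the 38.** For the between-factors routine, λ = f² × N × m / (1 + (m − 1)r), with 1 and N − 2 degrees of freedom.
- N = 38: λ = 0.1681 × 38 × 2 / 1.5 = 8.52, power 0.811.
- N = 36: power 0.788.

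So 38 is the smallest even N that reaches 80%. At f = 0.41 the within-between interaction routine returns 14, and a two-sided test on a single measure returns 50. Of the routines tried, only the between-factors one uses all the stated inputs and gives 38.

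**2. The same test with the effect where it can occur.** The difference is 0 m at baseline and 15 m at week 4, so the average is 7.5 m and f = 7.5 / (2 × 18.3) = 0.205.
- N = 38: λ = 0.0420 × 38 × 2 / 1.5 = 2.13, power 0.295.
- N = 44: power 0.335.
- 80% power needs 144 completers.

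**3. Group-by-time, equivalent to a t-test on change.** SD of change = 18.3 × √(2(1 − 0.5)) = 18.3 m, and λ = (15 / 18.3)² × N / 4.
- N = 38: λ = 6.39, power 0.691.
- N = 44: power 0.757.
- 80% power needs 50 completers (0.811).

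A simulation of 40,000 trials at N = 38 gave 0.294 for step 2 and 0.691 for step 3.

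**4. ANCOVA on week-4 distance, adjusted for baseline distance.** Residual SD = 18.3 × √(1 − 0.5²) = 15.8 m.
- N = 38: λ = (15 / 15.8)² × 38 / 4 = 8.52, power 0.810.
- N = 44: power 0.866.

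This nearly matches the plan's own figure because 1/(1 − r²) and 2/(1 + r) are both 1.33 at r = 0.5.

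**5. After the plan's own loss.** 44 × 0.8 = 35.2, so about 35 complete, not 38. Power is then 0.653 for group-by-time and 0.775 for ANCOVA.

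**6. Dependence on what 18.3 m means, at N = 38.**

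| 18.3 m taken as | r | Averaged group effect | Group-by-time | ANCOVA |
|---|---|---|---|---|
| SD of distance | 0.3 | 33% | 55% | 73% |
| SD of distance | 0.5 | 30% | 69% | 81% |
| SD of distance | 0.8 | 25% | 97% | 98% |
| SD of change | 0.3 | 44% | 69% | 86% |
| SD of change | 0.5 | 30% | 69% | 81% |
| SD of change | 0.8 | 13% | 69% | 74% |

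At the plan's r = 0.5 the two SDs coincide, so the main figures do not depend on which was meant.

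**The case against.** The strongest reply is that 30% belongs to a test the plan never calls decisive. The Statistical analysis section speaks of relationships between and within groups and adds post hoc comparisons. A two-way ANOVA also yields the interaction, and the target is framed as improvement. This stands in part. A reader might infer that the trial simply has 30% power, but the document does not commit to the averaged effect as the primary test, so group-by-time is the fairer reading. It still falls short, at 69% with 38 completers and 76% if all 44 complete.

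Three further inferences are tempting and are not supported:

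- **That an SD of 18.3 m is impossibly small for walking distance.** The figure is inferred, and a condensed article may leave its source to the full protocol. It may be the SD of change. At r = 0.8 that would correspond to a distance SD of 18.3 / √(2 × 0.2) = 28.9 m, with group-by-time power still 69%.
- **That power collapses under larger SDs.** Holding r at 0.5, ANCOVA power at 38 is about 41% for an assumed distance SD of 30 m and 25% for 40 m. At r = 0.8 these become about 70% and 47%, and at r = 0.9 about 93% and 73%. The document supports no particular SD, so a range that fixes r is one-sided.
- **That a 15 m result fails a 30 m threshold.** The section uses 30 m as the improvement expected with exercise alone. It sets no 30 m criterion for the difference between arms.

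It is also fair that the calculation reproduces. The fault is a mismatch between effect and test, not a slip in the sum.

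**Conclusion.** The concern holds. The 38 comes from a routine that averages over baseline, while f = 0.41 describes a difference expected only at week 4. With f = 0.41 and r = 0.5, power at 38 completers is about 69% for group-by-time and about 30% for the averaged group effect. At 44 the figures are 76% and 34%. Neither reading of the named ANOVA delivers the stated 80%, even with no loss.

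The figures assume equal arms in expectation at baseline, equal variance at both visits, a two-sided 5% test and the plan's r = 0.5. A higher correlation would lift group-by-time above 80% if 18.3 m is the SD of distance (97% at r = 0.8), but not if it is the SD of change. The plan fixed r at 0.5.

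A reader might conclude that more patients are required. That does not follow: a baseline-adjusted ANCOVA has about 81% at 38 completers on the same inputs. The article does not specify that analysis, so it is a remedy and not a defence of the present text.

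**What to change.** Keep 44 patients and revise the Sample size and Statistical analysis sections together.

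1. Name the primary contrast: the week-4 between-arm difference in 6MWT from an ANCOVA adjusted for baseline 6MWT. If that is not wanted, name the group-by-time test.
2. State the target as a 15 m difference between arms. Describe 30 m and 45 m as expected within-arm improvements, not as arm-specific MCIDs.
3. Give the SD behind f = 0.41 (18.3 m is implied) and its basis, and say whether it is the SD of distance or of change.
4. Restate power at 38 completers as about 81% (ANCOVA) or 69% (group-by-time), and at the roughly 35 left after 20% loss as about 78% or 65%.
5. If a sensitivity table is added, vary both the SD and r.

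The cost is protocol wording and a less favourable power statement. No extra patients, visits or measurements are needed, since baseline 6MWT is already collected. If group-by-time is kept as the primary test and 80% is still wanted, about 50 completers would be required.

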**Methods:**

This is a two-arm, prospectively registered, randomized trial with concealed allocation, double-blind, and intention-to-treat analysis. Forty-four patients with HFrEF will be recruited. The experimental group will undertake 25–30 min aerobic exercise training associated with tDCS, for 4 weeks. The control group will undergo the same aerobic exercise training, but with sham-tDCS. The primary outcome will be functional performance by the 6-min walk test. Secondary outcomes will include cardiopulmonary exercise capacity, inflammatory cytokines, and quality of life. Outcomes will be collected by a researcher blinded to group allocation at baseline (T0) and after 4 weeks of intervention (T1).

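### Enrolling 44 does not cover the stated 20% loss from a requirement of 38: it covers 6 losses (13.6%), and at 20% missing walk-test data power is about 78% rather than 80%

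*Protocol article*

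**What the plan says.** The Sample size section bases the calculation on six-minute walk distance and describes the inputs as "sample size calculations for the ANOVA two-way test between factors", run in G*Power 3.1. It reports that "The effect size calculation was 0.41" as Cohen's f, with α of 5%, a value of 80% printed as β, and "2 groups and 2 measurements, and correction between measurements of 0.5". The result is given as "A total of 38 volunteers were reached". The loss allowance follows: "with the possibility of sample loss of 20%, a sample of 44 participants was estimated", with 22 in each arm.

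The Methods part of the Abstract repeats the total: "Forty-four patients with HFrEF will be recruited". No other section gives a different loss rate or a different rule for inflating the sample.

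Two other sections bear on how much data may actually be lost. The Statistical analysis section says that walk-test and cytokine data will be collected from participants who stop or depart from the intervention. The section on trial retention describes session reminders and rescheduling within the week.

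**The concern.** One sentence gives a required number, a loss rate and an enrolment number, and the third does not follow from the first two. Going from 38 to 44 adds 6 participants. A 20% loss from 44 removes almost 9.

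A reader, or an ethics committee, would take the sentence to mean that the trial keeps its intended 80% power if one participant in five is lost. If 44 does not achieve that, either the enrolment figure was miscalculated or the stated allowance is too generous for it. The text should say which.

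**Working it through.** **Inputs** (all from the Sample size section): f = 0.41; α = 0.05; power 0.80 (my reading of the value printed as β); k = 2 groups; m = 2 measurements; correlation ρ = 0.5 (my reading of the word printed as correction); required N = 38; loss d = 20%; enrolled N = 44.

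**Step 1. Reproduce the 38.** G*Power's repeated-measures ANOVA for between factors uses a noncentral F distribution with 1 and N − 2 degrees of freedom and

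λ = f² × N × m / [1 + (m − 1)ρ] = 0.1681 × N × 2 / 1.5.

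| N | λ | Power |
|---|---|---|
| 34 | 7.62 | 76.3% |
| 35 | 7.84 | 77.6% |
| 36 | 8.07 | 78.8% |
| 37 | 8.29 | 79.95% |
| 38 | 8.52 | 81.1% |
| 44 | 9.86 | 86.6% |

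The smallest N that reaches 80% is 38, so the plan's base figure reproduces exactly. It leaves no slack: 37 already falls just below 80%.

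**Step 2. Inflate for a 20% loss.**
- Correct rule: N/(1 − d) = 38/0.80 = 47.5, so 48 (24 per arm). Check: 48 × 0.80 = 38.4.
- Common but incorrect rule: N × (1 + d) = 38 × 1.20 = 45.6, so 46. Check: 46 × 0.80 = 36.8, still below 38.

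Neither rule gives 44, so rounding or choice of convention does not explain the figure.

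**Step 3. What 44 covers.**
- Losses allowed: 44 − 38 = 6.
- As a loss rate: 6/44 = 13.6%.
- As an increase over the requirement: 6/38 = 15.8%, also not 20%.

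**Step 4. What a 20% loss leaves.** 44 × 0.80 = 35.2, so about 35 analysed, 3 fewer than required. From the table, power is 77.6% at 35, and 78.8% at 36 (18 per arm). The gap to 80% is 2.4 points at 35 and 1.2 points at 36.

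**The case against.** The strongest reply is that the discrepancy hardly matters. A gap of 1 to 2.5 power points is minor beside the uncertainty in the effect size itself, since the 45 m gain assumed for the experimental arm was chosen empirically. That stands as a comment on size. It does not make the sentence correct.

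A second reply is that stopping the intervention is not meant to be loss from the primary analysis. Walk-test data are to be collected after discontinuation, the analysis is by intention to treat, and there are retention measures. This also stands in part. It makes 35 analysed participants a worst case, reached only if the whole 20% has no walk-test result. But the Sample size section does not use this provision to justify 44, and the provision cannot supply data for someone who never returns for the four-week assessment.

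A reader might also infer something stronger: that attrition leaves the group-by-time comparison badly underpowered, at about 65%. The documents do not support that figure. It comes from treating 0.41 as the effect size of a two-group test on change scores (λ = f² × N = 0.1681 × 35 = 5.88, power 65.3%). The protocol does not say that 0.41 has this meaning, and it gives no standard deviation from which the meaning could be recovered. The same inputs in the standard within-between interaction formula (λ = f² × N × m/(1 − ρ) = 0.1681 × 35 × 2/0.5 = 23.5) give 99.7%. Even on the change-score reading, power at the full 38 is only 69%, so most of that gap would come from the choice of test and little from attrition.

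**Conclusion.** The sentence is wrong as it stands. A requirement of 38, a loss of 20% and an enrolment of 44 cannot all be true together. For 38 to remain after a 20% loss, enrolment must be 48; an enrolment of 44 covers a 13.6% loss. The error is confined to the step from 38 to 44, because the 38 itself reproduces.

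The size is modest: 4 participants in enrolment or, if 44 is kept and 20% have no walk-test data, power of about 78% in place of 80%. With 6 or fewer missing, 44 meets the target.

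This rests on accepting f = 0.41, the between-factors test and a correlation of 0.5 as stated, and on reading the 20% as participants without primary outcome data. Whether that test and effect size suit the hypothesis is a separate question. The finding does not show that the trial is seriously underpowered.

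**What to change.** Keep 44 and replace the loss sentence in the Sample size section with:

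> 44 allows for 6 participants (13.6%) without primary outcome data; if 20% are missing, about 35 are analysed and power is about 78% on these inputs.

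This costs one sentence and a slightly less favourable statement. Design, conduct and analysis do not change, and the total in the Abstract stays as it is.

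If the sponsor prefers to keep the 20% allowance, enrolment becomes 48 (24 per arm). That costs four more participants, and the total must then be changed in both the Sample size section and the Abstract.

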### Recruitment

We will use the expanded form of recruitment, by free demand, through dissemination in the media (ads on social networks, radio, and television), from which we will be able to have user representatives from different health units. We will visit medical units that are references to treatment for heart failure in the city of Manaus, Amazonas, and will deliver flyers with information about the project, and telephone numbers to contact the researchers. Once the eligibility criteria are met, they will be able to participate in the study.

### Strategies for trial retention

At the beginning of the training, all participants will be instructed on the importance of exercises for their health as a medical education strategy, as well as to encourage adherence to the program. The day before each session, every participant will receive a reminder message via cell phone confirming the date and time. Absences can be circumvented by rearranging the schedules within the same week.

### Randomization

The randomization list will be generated electronically by group statisticians, with a random number of blocks consisting of 4 to 6 participants per block. The randomization list will be generated in the statistical software R version 3.6.3 (Project R for statistical computing), using the blockrand package. The randomization process will be carried out by an external researcher not involved in the study, who will generate the randomization list on the computer. The same investigator will be responsible for maintaining and protecting allocation confidentiality and, in addition, will keep a copy of the list in a place inaccessible to participants and research staff. Participants will be allocated to intervention groups through codes generated by the software. To avoid possible errors and misguidance, random numbers will be documented with “I” for intervention and “C” for control. This process will be recorded to ensure that the envelopes are sealed with the respective names of the participants. All envelopes will be coated with aluminum foil to prevent possible reads through transparency. The allocation sequence will be blinded to researchers, investigators, and study participants. The allocation of participants to the intervention groups will only be revealed after the individual signs the informed consent, thus ensuring that the status of the group is not known during the study. In case of risk to the patient, the masking will be undone.

### Statistical analysis

Exploratory analyses will be carried out allowing a survey of the frequency distribution and calculation of means and standard deviations. The 95% confidence intervals will be considered, and effect sizes will be calculated for primary and secondary outcomes. Statistical significance will be stipulated with *p*<0.05. The Shapiro-Wilk test will be applied to analyze the normality of the sample distribution; unpaired *t*-test will be used for numeric variables, comparing means between two groups; and Fisher’s exact test will be used for categorical variables. Two-way ANOVA for between factors accompanied by post hoc Bonferroni analysis will be used to measure and predict the degree of relationship between inter- and intragroup variables. Pearson correlation will be performed to test the association between two continuous variables, and multiple linear regression will be used to quantify the relationship between predictor variables and the outcome variable. For data analysis, the statistical programs Jamovi (Jamovi Project, Sydney, Australia) and GraphPad Prism 7.0 (GraphPad, CA, USA) will be used. We will not perform sub-analysis, mainly because the primary stage is well defined in relation to the central question. Furthermore, it may be necessary to perform adjusted calculations for some variables, such as age, weight, BMI, EF%, and β-blocker drug dose. For this purpose, the utilization of these variables as covariates will be used in the ANOVA two-way analysis described above.

Participants who discontinue or deviate from intervention protocols will have their data on 6MWT and inflammatory cytokines collected.

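### The two-way ANOVA is labelled as having between factors and names no within-patient factor, so the 6MWT treatment test is badly fixed under either reading of the label

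*Protocol article*

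**What the plan says.** The Statistical analysis section of the protocol article gives the main model in one sentence: "Two-way ANOVA for between factors accompanied by post hoc Bonferroni analysis will be used". That sentence says the model is to address the "relationship between inter- and intragroup variables", so comparisons between arms and within arms are both to come from it. Adjusted analyses use the same model: "the utilization of these variables as covariates will be used in the ANOVA two-way analysis described above". The section does not describe any factor as repeated, within-patient or paired, and it does not say which effect of the ANOVA is the treatment effect.

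The Sample size section uses almost the same label, "sample size calculations for the ANOVA two-way test between factors", but lists as inputs "2 groups and 2 measurements, and correction between measurements of 0.5". The effect it plans for is a difference in improvement on the 6MWT. The control arm is given a 30 m gain, and for the other arm "we chose 45 m of physical capacity improvement as the MCID to the experimental group". The Intervention section confirms that the same patients are assessed at T0 and at T1, four weeks later.

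**The concern.** With two arms and two visits, the natural factors of a two-way ANOVA are arm and visit, and visit varies within the patient. A two-way ANOVA in which both factors are between-subject is the factorial model for independent observations. Someone choosing a procedure in Jamovi or GraphPad Prism from this sentence has to decide between an ordinary and a repeated-measures ANOVA, and the printed label points to the ordinary one. The Sample size section points to the other.

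The choice matters because the two models give different error terms for the same data. The label also leaves open which effect carries the trial's question. That question is whether patients improve more with active stimulation, which is a difference in change and not a difference in level averaged over both visits. The secondary outcomes and the covariate-adjusted analyses inherit the same ambiguity if they go through the same model.

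**Working it through.** **Inputs.** From the Sample size section: Cohen's f = 0.41, α = 0.05, power 80% (printed as β), 2 groups, m = 2 measurements, ρ = 0.5 (the printed word is read as correlation), gains of 30 m and 45 m, total N = 38 before losses. Allocation is 1:1, so n = 19 per arm.

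**Step 1. Reproduce the stated 38.** For the between-factors test of a repeated-measures ANOVA, the noncentrality is λ = f²·N·m / [1 + (m−1)ρ], with 1 and N−2 df.

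- N = 38: λ = 0.1681 × 38 × 2 / 1.5 = 8.52, power 0.811.
- N = 36: λ = 0.1681 × 36 × 2 / 1.5 = 8.07, power 0.788.

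The target is first met at 38, as printed. The alternatives do not give 38: the same test with ρ = 0 needs 26 patients, a factorial ANOVA on independent observations needs 49 to 50 observations, and the repeated-measures interaction with f = 0.41 needs 14 patients. The trial was therefore sized on a model with within-patient correlation.

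**Step 2. Implied SD.** With two equal groups d = 2f = 0.82, so SD = 15 / 0.82 = 18.3 m. The protocol states no SD. At ρ = 0.5 the SD of change is √[2(1−0.5)] = 1 times the single-visit SD, so taking 0.82 in either unit gives the same result. Equal expected baselines are assumed below.

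**Step 3. Literal reading: visits treated as independent rows.** There are 76 rows and 4 cell means, hence 72 residual df instead of 36.

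- Arm main effect: naive/true variance = 1/(1+ρ) = 1/1.5. Type I error ≈ 2[1 − Φ(1.96/√1.5)] = 11.0%.
- Arm-by-visit: naive/true variance = 1/(1−ρ) = 2, so the standard error is 1.41 times too large. Type I error ≈ 2[1 − Φ(1.96/√0.5)] = 0.6%; about 0.7% by simulation.
- T1-only comparison between arms: about 5% by simulation, so essentially valid.
- Power of arm-by-visit for 15 m: naive SE = 2 × 18.3/√19 = 8.4 m, true SE = 18.3 × √(2/19) = 5.9 m, critical t (72 df) = 1.99. Power ≈ Φ[(15 − 1.99 × 8.4)/5.9] ≈ 39%; simulation agrees (39 to 40%).

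**Step 4. Reading in line with the Sample size section: between-factors test of a repeated-measures ANOVA.** This compares the arms on the mean of T0 and T1. If the arms are equal at T0 and differ by 0.82 SD at T1, the averaged difference is 0.41 SD, and the SD of the average is √[(1+0.5)/2] = 0.866. λ = (0.41/0.866)² × 19/2 = 2.13, power 0.295.

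**Step 5. Tests aimed at the planned effect, N = 38.**

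- Within-patient change (the arm-by-visit interaction of a mixed ANOVA): λ = 0.82² × 19/2 = 6.39, power 0.691.
- T1 adjusted for T0: residual SD √(1−0.25) = 0.866, λ = (0.82/0.866)² × 19/2 = 8.52, power about 0.81.

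**Step 6. Range over ρ** (d = 0.82 in single-visit SD units; only ρ = 0.5 is in the protocol):

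| ρ | Type I error, arm effect, independent rows | Type I error, arm-by-visit, independent rows | Power, arm-by-visit, independent rows | Power, average of T0 and T1 | Power, change | Power, T1 adjusted for T0 |
|---|---|---|---|---|---|---|
| 0.3 | 8.6% | 1.9% | 41% | 33% | 55% | 73% |
| 0.5 | 11.0% | 0.6% | 39% | 30% | 69% | 81% |
| 0.8 | 14.4% | about 0.001% | 35% | 25% | 97% | 98% |

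The type I entries are the large-sample formulas; simulation with 19 per arm gives slightly larger values for arm-by-visit (0.7% at ρ = 0.5, about 0.01% at 0.8).

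**The case against.** A reader might infer that the plan treats the two visits as independent and that every standard error for the 6MWT is therefore wrong. The documents do not support that. A number of measurements and a correlation between them have no place in an ANOVA of independent rows, yet the Sample size section enters both under nearly the same label, and of the variants tried only a model with that correlation gives the printed 38. The simpler reading is that both sections mean the between-group test of a repeated-measures ANOVA. Nowhere does the article say that T0 and T1 are independent, and the analysis sentence expressly includes within-group comparisons. The unpaired t-test and Fisher's exact test are no evidence either way, since patients in different arms are independent. Even under the literal reading, the T1 comparison between arms, a natural post hoc contrast, keeps about 5% type I error.

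All of that stands. It limits the point but does not remove it. The favourable reading repairs the standard errors and leaves a test of the wrong contrast, with about 30% power for the difference the trial was planned on. It could also be said that an article leaves model details to a fuller plan. Here, though, the article does name the model, and the name it gives misleads under one reading and misses the planned effect under the other.

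**Conclusion.** The point holds as a badly fixed analysis model. It does not establish that the visits are planned to be treated as independent. At the protocol's own correlation of 0.5 and 19 per arm, power for the 15 m difference in gain is about 39% if rows are taken as independent and about 30% if the arms are compared on the average of T0 and T1, against 69% for a test on within-patient change. The type I errors of about 11% and 0.7% apply to the literal reading only. The stated N = 38 is reproduced and is not disputed here.

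The power figures assume equal expected baselines and 0.82 as the 15 m difference in SD units, hence an SD of 18.3 m that the protocol does not state. With a larger SD all the powers fall. For any positive correlation the averaged test remains weaker than the change test, because the ratio of their standardised effects is √[(1−ρ)/(1+ρ)], or 0.58 at ρ = 0.5.

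**What to change.** In the Statistical analysis section, replace the between-factors label by: two-way mixed ANOVA with arm as the between-patient factor and visit (T0, T1) as the within-patient repeated factor. In the same place:

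- State which single effect is the treatment effect for the 6MWT. It can be the arm-by-visit interaction, that is, the difference in change. It can instead be the arm difference at T1 adjusted for T0. These are separate options and not equivalent (about 69% and 81% power at ρ = 0.5), so one must be chosen in advance, before unblinding.
- State that the T0 to T1 post hoc comparisons within arms are paired.
- Apply the same model to the cardiopulmonary, cytokine and quality-of-life outcomes, and to the covariate-adjusted analyses.

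The cost is a sentence or two. No data collection, visit or patient is affected.
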